## Supplementary appendix

1. Sensitivity Analysis – Missing Data
2. Per-Protocol Analysis
3. Subgroup Analysis
4. Figures
5. Tables
6. Protocol

p.1

p.2

p.3

p.3
p.8
p.11

1. Sensitivity Analysis - Missing Data

In this section, we present two sensitivity analyses to examine the robustness of our conclusions from the primary analysis. Our primary analysis was performed using a complete case analysis, which assumes the data is missing at random (MAR), i.e. the unobserved data is from the same conditional distribution as the observed data. This seems to be a plausible assumption for this trial as the numbers lost to follow-up are reasonably low, there are roughly equal numbers of missing data across both arms. Whilst there is an imbalance of withdrawals across the two arms (more in the intervention), the numbers are small and the actual reasons for withdrawal seem to be mostly unrelated to the intervention.

Our two sensitivity analyses are:

- Impute quantiles. For each missing data point, impute the median value of the arm that patient belongs to and analyse using ANCOVA adjusting for baseline, minimisation factors and treatment allocation. Repeat the analysis on a population that has the 60th quantile imputed for one arm’s missing values and the 40th quantile for the other, then again using the 70th and 30th quantiles. We repeat the process but flipping the arms. In total 5 sensitivity analyses will be performed and the results will be displayed graphically. Due to the level of missingness (>20%), imputing values beyond the 70th and 30th quantiles will start to become meaningless as this will distort the data to an unhelpful degree.

- Multiple Imputation by Chained Equations.

The first sensitivity is to test the MAR assumption, by imputing different values for each arm’s missing data we examine how the treatment effect is affected by breaking the MAR assumptions to varying degrees. Multiple imputation using the analysis model assumes MAR (just as complete case analysis does) so the second analysis does not test this assumption. The second analysis, using multiple imputation, is included at the request of the DSMC and TSC for completeness and to back-up the main analysis’s findings.

The intention-to-treat analysis strategy used is a comprehensive examination of the conclusions drawn from the main analysis. For clarity, eTable 1 shows the values being imputed for each quantile for both Systolic and Diastolic Blood Pressure for the first sensitivity analysis.

In eFigure 1 and 2, we can see how the estimates of the adjusted mean difference change depending on the values we impute. As we use lower values to impute for the intervention arm and higher values in the control arm, the effect size creeps towards favouring the intervention, as one would expect. The opposite is also true, lower values in the control and higher values in the intervention makes the mean estimate trend towards favouring the control arm. When we impute the 70th quantile for the intervention and 30th quantile for the control we yield a statistically significant result favouring the control arm to a 5% significance level for both Systolic and Diastolic Blood Pressure.

This sensitivity analysis tells us that we would need to see a large violation of the MAR assumption assumed in the main analysis to render the results invalid and, given the reasons for missingness in the TEPHRA trial, this departure being a reality is unlikely.

For our second sensitivity analysis on missing data, we performed Multiple Imputation by Chained Equations (MICE). This method is widely used in research due to its ability to account for statistical uncertainty caused by the imputations by pooling multiple imputations and its flexibility to handle variables of varying types (binary or continuous). In our imputations, we have imputed using variables from our analysis model and not included other variables that may predict missingness. In this analysis we used 40 multiple imputations, analysed each “complete” dataset separately then pooled the results using the pool command from the mice package in R which averages the estimates of the complete data model, computes the total variance over the repeated analyses by Rubin’s rules (Rubin, D.B. (1987). Multiple Imputation for Nonresponse in Surveys. New York: John Wiley and Sons). Using 40 imputations minimises the error caused by the imputation process. We present the results as we did with the primary analysis - in eTable 2 and eFigure 3. As we have complete data for the primary outcome at baseline, no imputation was necessary and has been included in the eTable 2.

The results from this sensitivity analysis using Multiple Imputation by Chained Equations are very similar to the results from the primary analysis. The main, null, result from the study is shown to be a robust result when looking at departures from the MAR assumption and different approaches when handling missing data.

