#### 2. Per-Protocol Analysis

A sensitivity analysis on the primary outcome has been carried out on a per-protocol basis to examine robustness of conclusions to different assumptions about departures from randomised policies. The target intervention exposure was 3 aerobic sessions per week, completed on separate days, for 16 weeks, with a compliance threshold set at 80%; equivalent to ≥ 39 independent aerobic exposures with no greater than 2 weeks between exposures. Before recruitment commenced a compliant session was defined as a supervised exercise session, but during the course of the trial this definition was relaxed to include unsupervised sessions captured using the activity monitor. The same mixed model was used for the primary outcomes accounting for person random effects, baseline (as a continuous covariate) and 4-month blood pressure values (or peak oxygen uptake), gender, age (<24, 24–29, >30 years old), and gestational age (<32, 32-37, >37 weeks) as fixed effects with treatment by 16 week time point interaction also included was used to analyse 24 Hour Awake Ambulatory Blood Pressure (Systolic and Diastolic) on the per-protocol population. The results are presented in eTable 3, nonparametric 95% confidence intervals around the unadjusted mean difference and p-values are not presented. The results from the per-protocol analysis reinforce the interpretation of the main trial results: that there is no difference between the Control and Exercise Intervention groups in 24 Hour Awake Ambulatory Blood Pressure at 16 or 52 weeks post-randomisation.

3. Subgroup Analysis

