**5. TABLES**

| Quantiles | Systolic Blood Pressure |  | Diastolic Blood pressure |  |
| --- | --- | --- | --- | --- |
|  | Intervention | Control | Intervention | Control |
| 30 | 120 | 121 | 72 | 71 |
| 40 | 124 | 124 | 74 | 72 |
| 50 | 125 | 126 | 75 | 75 |
| 60 | 129 | 128 | 76 | 77 |
| 70 | 131 | 130 | 80 | 79 |

eTable 1. This table shows the values imputed for each quantile for both Systolic and Diastolic Blood Pressure for the first sensitivity analysis.

eTable 2. Sensitivity analysis using MICE

|  | Exercise Intervention | | Control | | Mean Difference (95%) | |
| --- | --- | --- | --- | --- | --- | --- |
|  | n | Mean (SD) | n | Mean (SD) | Unadjusted | Adjusted |
| **24 Hour Awake Ambulatory Systolic Blood Pressure** | | | | | |  |
| Baseline | 102 | 129.1 (9.3) | 101 | 128.3 (8.7) | - | - |
| 16 Weeks | 102 | 126.6 (11.3) | 101 | 126.0 (10.0) | 0.6 (0,1) | 0.0 (-2.6,2.7) |
| **24 Hour Awake Ambulatory Diastolic Blood Pressure** | | | | | |  |
| Baseline | 102 | 77.0 (6.4) | 101 | 77.4 (7.5) | - | - |
| 16 Weeks | 102 | 76.4 (6.9) | 101 | 75.6 (6.7) | - 1. (0,1) | 1. (-0.9,2.9) |

eTable 3. Per-protocol analysis

|  | Exercise Intervention | | Control | | Mean Difference (95%) | |
| --- | --- | --- | --- | --- | --- | --- |
|  | n | Mean (SD) | n | Mean (SD) | Unadjusted | Adjusted |
| **24 Hour Awake Ambulatory Systolic Blood Pressure** | | | | | | |
| Baseline | 82 | 129.41 (9.46) | 101 | 128.25 (8.68) | - | - |
| 16 Weeks | 71 | 126.93 (11.58) | 84 | 125.83 (10.00) | 1.10 | 0.02 (-2.87,2.92) |
| 52 Weeks | 63 | 127.81 (13.11) | 69 | 125.52 (11.82) | 2.30 | 1.52 (-1.61,4.65) |
| **24 Hour Awake Ambulatory Diastolic Blood Pressure** | | | | | | |
| Baseline | 82 | 77.48 (6.19) | 101 | 77.36 (7.46) | - | - |
| 16 Weeks | 71 | 76.51 (7.04) | 84 | 75.54 (6.73) | 0.97 | 0.61 (-1.41,2.64) |
| 52 Weeks | 63 | 77.01 (8.32) | 69 | 75.24 (7.76) | 1.77 | 1.31 (-0.88,3.49) |

eTable 4. Subgroup comparison of 24 Ambulatory Blood Pressure (mmHg) and Peak Oxygen Uptake (ml/kg/min) according to Volume of Weekly Supervised Exercise Completed.

|  | Exercise Intervention | | | Control | | Mean Difference (95%) | | | |
| --- | --- | --- | --- | --- | --- | --- | --- | --- | --- |
|  | n | Mean (SD) | | n | Mean (SD) |  | | | Adjusted |
| **24 Hour Awake Ambulatory Systolic Blood Pressure** | | | | | | | |  | |
| **Weekly Exercise Supervision ≥ 3 hours** | | | | | | | | | |
| Baseline | 45 | 129.6 (9.0) | | 101 | 128.3 (8.7) |  | | | |

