### Physical Examination (15 mins)

Assessments including body composition measures, height, weight, BMI, waist to hip ratio, gait analysis, and resting blood pressure will be taken. Participants will undergo a brief gait analysis by completing a monitored 10 meter walk while wearing an accelerometer fastened to their low back. Participants will have their blood pressure checked after 5 minutes rest using the automated mode of a sphygmomanometer. 3 blood pressure readings will be taken at intervals of 1 minute. The first reading will be discarded and not used toward the mean blood pressure calculated for the visit.

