# STATISTICS AND ANALYSIS

## Description of Statistical Methods

The analysis will be carried out on the basis of intention-to-treat (ITT). This is, after randomisation, participants will be analysed according to their allocated intervention group irrespective of what they actually receive.

Patient demographic characteristics and other baseline information will be summarised by treatment group. Numbers (with percentages) for binary and categorical variables and mean (standard deviation), or median (interquartile or full range) for continuous variables will be presented. Normality of variables will be assessed by visual assessment of the normality curves and the Shapiro-Wilk test. The analysis of the primary outcome will be assessed using analysis of covariance (ANCOVA) adjusting for baseline values and minimisation factors used in the randomisation process. Results will be presented as adjusted mean difference in change in ambulatory blood pressure between randomised groups at 4 months with 95% confidence intervals (CI) and associated two-sided p value. The analysis of secondary outcomes will also be done using analysis of covariance (ANCOVA) to establish a co-variant model to examine the effect of cardiac structure, vascular function and lifestyle behaviours on exercise capacity. Outcomes measured on more than one occasion will be analysed using a mixed effects model. The data collected from the sub-study will be analysed using paired and independent T-test. If the model assumptions are not met and evidence of departure from Normality is observed, transformations of the data will be employed or non-parametric tests will be carried out. Statistical analysis will be carried out using STATA or SPSS statistical software.

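### The multiple imputation used only analysis-model variables, so its agreement with the complete-case result is no evidence of robustness, and the stated case for MAR fits poorly with the trial's own counts

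*Supplement*

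**What the plan says.** Supplement section 1 (Sensitivity Analysis - Missing Data) describes a complete-case primary analysis that assumes MAR. It defends the assumption on the grounds that "the numbers lost to follow-up are reasonably low, there are roughly equal numbers of missing data across both arms", and adds that people mostly left for reasons that had little to do with the intervention. It also puts missingness above 20% and acknowledges more withdrawals in the exercise arm.

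Two checks follow. One imputes single arm-specific quantiles, from the median out to the 70th and 30th. The other is MICE with 40 imputations, in which "we have imputed using variables from our analysis model and not included other variables that may predict missingness". The section says openly that MICE does not test MAR and was added at the request of the oversight committees. Its closing paragraph nevertheless cites the closeness of the MICE result and calls the null finding robust both to departures from MAR and to the method of handling missing data.

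Which analysis model is meant is not settled. The protocol (Description of Statistical Methods) plans "analysis of covariance (ANCOVA) adjusting for baseline values and minimisation factors used in the randomisation process". Supplement section 2 says "The same mixed model was used for the primary outcomes accounting for person random effects, baseline (as a continuous covariate) and 4-month blood pressure values", and eTable 3, from that model, includes 52-week results.

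**The concern.** If the imputation model holds the same variables as the analysis model and only the outcome is missing, the imputed values come from the regression already fitted to the complete cases. Agreement is then close to automatic and tells the reader nothing about the people who are missing.

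This matters because the tables point to variables that could carry information. In the exercise arm, missingness is concentrated among those with low exposure to the intervention. A good number of people without ambulatory pressure still attended Visit 2, where clinic pressure is scheduled: "3 blood pressure readings will be taken at intervals of 1 minute". At stake are the credibility of the written MAR defence and the weight a reader gives to the robustness statement. The sign of the primary result is not at stake on present evidence.

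**Working it through.** **Inputs.** eTable 2: 102 exercise and 101 control at baseline; MICE adjusted differences of 0.0 (-2.6 to 2.7) systolic and 1. (-0.9 to 2.9) diastolic. eTable 3: per-protocol exercise 82 at baseline and 71 at 16 weeks; control 84 at 16 weeks. eTable 4: exercise volume of 3 h/week or more, 45 falling to 43; below 3 h/week, 57 falling to 33; peak oxygen uptake at 16 weeks for 45 + 39 exercise and 92 control participants. I treat the 20 exercise participants outside the per-protocol set as non-compliant.

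1. **Overall missingness.** Exercise: 102 - (43 + 33) = 26 (25.5%). Control: 101 - 84 = 17 (16.8%). Total: 43/203 = 21.2%, which reproduces the stated level above 20%. Fisher exact test between arms: p = 0.17.

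2. **Missingness within the exercise arm.** Inside the per-protocol set: 82 - 71 = 11 of 82 (13.4%). Outside: 26 - 11 = 15 of 20 (75%), Fisher p about 2 × 10⁻⁷. By volume: 24 of 57 (42.1%) below 3 h/week against 2 of 45 (4.4%) at or above, p about 8 × 10⁻⁶. The analysed exercise group is therefore 71 of 76 per-protocol. The per-protocol analysis shares those 71 people and all 84 controls with it, so its agreement is also largely guaranteed.

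3. **Does MICE add anything?** A simulation used the observed missingness pattern (24/57, 2/45, 17/101), 400 runs and 40 imputations. Low-volume participants were assumed to differ in 16-week pressure, given baseline, by γ; the true treatment effect was 0.

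| Assumed γ (mmHg) | Complete case | MI, analysis-model variables | MI plus compliance |
|---|---|---|---|
| 5 | -0.58 | -0.58 | 0.04 |
| 10 | -1.24 | -1.24 | 0.03 |

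4. **How large is the link in the trial's own data?** Standardise the eTable 4 adjusted effects to the randomised mix.
   - Systolic: observed mix (43 × -0.1 + 33 × 0.3)/76 = 0.07; randomised mix (45 × -0.1 + 57 × 0.3)/102 = 0.12; shift +0.05 mmHg.
   - Diastolic: (43 × 0.9 + 33 × 0.3)/76 = 0.64; (45 × 0.9 + 57 × 0.3)/102 = 0.56; shift -0.07 mmHg.
   - Range: the shift is (57/102 - 33/76) × γ = 0.125γ. Residual SDs of about 9.2 and 6.4, backed out of the eTable 3 intervals, give approximate 95% ranges for γ of -3.8 to 4.6 (systolic) and -3.5 to 2.3 (diastolic). The shifts are then about -0.5 to +0.6 and -0.4 to +0.3 mmHg.

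5. **Tipping points.** Move only the 26 missing exercise values by δ and hold the MICE interval width. The estimate moves by (26/102)δ = 0.255δ.
   - Significance favouring control: 2.6/0.255 = about +10.2 mmHg systolic; 0.9/0.255 = about +3.5 mmHg diastolic.
   - Significance favouring exercise: 2.7/0.255 = about -10.6 systolic; 2.9/0.255 = about -11.4 diastolic.
   - Producing the 5 mmHg design effect for systolic pressure: 5/0.255 = about -19.6.

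6. **Auxiliary data.** Peak oxygen uptake at 16 weeks exists for 84 exercise and 92 control participants, ambulatory pressure for 76 and 84. At least 8 + 8 = 16 of the 43 with a missing outcome therefore attended Visit 2.

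7. **The quantile check.** By eTable 1, the 70/30 scenario sets missing systolic values 6 mmHg above the exercise median and 5 below the control median. Relative to median imputation, the raw difference moves by 6 × 26/102 + 5 × 17/101 = 1.53 + 0.84 = 2.4 mmHg. The MICE half-width is (2.7 + 2.6)/2 = 2.65. The reported significance of that scenario may thus owe something to single imputation, which understates the standard error.

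**The case against.** A reader might infer from the compliance counts that MAR is contradicted and that the primary result is biased. The documents do not support this. Compliance must also predict 16-week pressure given baseline, and eTable 4 shows little sign that it does. The association is also partly built in: section 2 defines compliance as at least 39 sessions with no gap beyond two weeks, so anyone who leaves early is non-compliant by definition and tends to lack the outcome as well. Low volume is likewise partly a result of withdrawal. These objections stand. Their limit is that the volume split is post hoc and imprecise, and only 5 people outside the per-protocol set were observed.

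A reader might also infer that 52-week ambulatory pressure was certainly left out of the imputation. That depends on whether the model was the ANCOVA or the mixed model, and the text supports either. Nor do the tables show how many of the 43 have a 52-week value.

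The authors do provide a check aimed at MAR departures, and they report its unfavourable 70/30 result openly. That is fair. However, they set the scenario aside as unlikely because of the reasons for missingness, which is the premise the counts in step 2 call into question.

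Finally, 26 against 17 is compatible with chance, and the section itself discloses both the level and the withdrawal imbalance. The complaint about "there are roughly equal numbers of missing data across both arms" is therefore mainly one of wording.

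**Conclusion.** The point holds as a moderate one. If MICE was restricted to the ANCOVA variables, its agreement with the complete-case estimate is expected and should not be offered as support for robustness. The written justification for MAR fits poorly with 21% missing overall and with 75% against 13% missing by per-protocol status.

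Nothing in the documents shows that the null result would change. The correction implied by eTable 4 is under 0.1 mmHg and about 0.6 mmHg at the edge of its range, against a design effect of 5 mmHg. A hidden benefit of that size would need missing exercise values about 20 mmHg lower. The more exposed direction is towards control, where about +3.5 mmHg in the missing diastolic values would reach significance. These sizes assume that the eTable 4 strata also describe the people who are missing, that control values are missing at random, and that the MICE interval width would not change. The effect of adding clinic or 52-week pressure cannot be computed, because no correlations are given.

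**What to change.** - Rerun MICE separately by arm. Add 16-week clinic blood pressure and peak oxygen uptake in both arms, and exercise volume in the exercise arm, noting that only 5 people outside the per-protocol set are observed.
- State whether the analysis model was ANCOVA or the mixed model. If it did not use 52-week ambulatory pressure, add that as an auxiliary variable.
- Replace the single quantile imputation with delta-adjusted multiple imputation that varies the exercise arm's missing values in both directions, far enough to pass the tipping points in step 5. Drawing those values from the control arm is not a substitute: it pulls the effect towards zero and so cannot challenge a null result.
- Report missing counts by arm and by compliance in place of the present description, and note that early leavers count as non-compliant.
- Reword the closing statement so that the present MICE analysis is not cited as evidence of robustness to departures from MAR.

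The cost is reanalysis and a few sentences. No new data are needed, provided clinic pressure was recorded at Visit 2 as the protocol schedules.

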#### 2. Per-Protocol Analysis

A sensitivity analysis on the primary outcome has been carried out on a per-protocol basis to examine robustness of conclusions to different assumptions about departures from randomised policies. The target intervention exposure was 3 aerobic sessions per week, completed on separate days, for 16 weeks, with a compliance threshold set at 80%; equivalent to ≥ 39 independent aerobic exposures with no greater than 2 weeks between exposures. Before recruitment commenced a compliant session was defined as a supervised exercise session, but during the course of the trial this definition was relaxed to include unsupervised sessions captured using the activity monitor. The same mixed model was used for the primary outcomes accounting for person random effects, baseline (as a continuous covariate) and 4-month blood pressure values (or peak oxygen uptake), gender, age (<24, 24–29, >30 years old), and gestational age (<32, 32-37, >37 weeks) as fixed effects with treatment by 16 week time point interaction also included was used to analyse 24 Hour Awake Ambulatory Blood Pressure (Systolic and Diastolic) on the per-protocol population. The results are presented in eTable 3, nonparametric 95% confidence intervals around the unadjusted mean difference and p-values are not presented. The results from the per-protocol analysis reinforce the interpretation of the main trial results: that there is no difference between the Control and Exercise Intervention groups in 24 Hour Awake Ambulatory Blood Pressure at 16 or 52 weeks post-randomisation.

3. Subgroup Analysis

Subgroup analysis as per Gestational Age (divided using the cut-offs defined in the minimisation procedure: < 32 Weeks, 32 - 37 weeks, > 37 Weeks) and Sex (Male and Female). The analysis has been performed through fitting a linear model adjusting for baseline and minimisation factors and fitting an interaction term between treatment allocation and the variable being subsetted (gestational age and sex in two separate analyses). Complete case analyses have been performed and the numbers in each subgroup from the complete case population are reported in the forest plot in eFigure 4. Subgroup analysis looking at subgroups on BMI, Glucose Level, Arterial Stiffness and Left Ventricular Mass (from MRI sub-study). The cut-offs have been determined through taking the ceiling of the median at baseline for each variable with the exception of Glucose; as this variable has a much smaller range the cut off is the median rounded to one decimal place. A complete cases analysis has been performed and the numbers in each subgroup is reported. Post-hoc exploratory sub-group analysis was also performed to understand whether there was difference in effect related to volume of supervised or unsupervised exercise sessions completed (above or below 3 hours per week) presented in eTable 4.

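### The per-protocol set appears to drop non-compliers from the exercise arm only, under a definition relaxed mid-trial, and reuses 155 of 160 observed participants, so it cannot reinforce the main result

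*Supplement*

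**What the plan says.** Section 2 of the supplementary appendix (Per-Protocol Analysis) presents this as a sensitivity analysis of the primary outcome. The exercise target is three aerobic sessions a week, on different days, over the 16-week programme. The rule for meeting it reads: "with a compliance threshold set at 80%; equivalent to ≥ 39 independent aerobic exposures with no greater than 2 weeks between exposures". Only supervised sessions counted under the rule set ahead of recruitment. The section then reports that "during the course of the trial this definition was relaxed to include unsupervised sessions captured using the activity monitor". The model adjusts for baseline value, gender, age group and gestational-age group. The section concludes: "The results from the per-protocol analysis reinforce the interpretation of the main trial results".

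The systolic rows give the numbers in each arm. In eTable 3 (per protocol) the row begins "Baseline | 82 | 129.41 (9.46) | 101 | 128.25 (8.68". In eTable 2 (all randomised, multiple imputation) it begins "Baseline | 102 | 129.1 (9.3) | 101 | 128.3 (8.7".

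The protocol describes the trial as open (Trial Design), bases the analysis on intention to treat (Description of Statistical Methods), and gives controls educational material only (Interventions, Comparison Group). No compliance rule for controls is stated. The supplement gives no date or reason for the relaxation, no number compliant under the supervised-only rule, and no result under it.

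**The concern.** There are three linked problems.

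1. **One-sided exclusion.** If compliance can be failed only in the exercise arm, people who would not have adhered leave that arm and stay in the control arm. Selected exercisers are then compared with all controls. The covariates in the model are not chosen as predictors of adherence, so the contrast rests on an assumption of no unmeasured confounding rather than on randomisation.
2. **A moved definition.** The rule set before recruitment counted supervised sessions, which is the intervention the protocol describes. Relaxing it in an open trial, without showing the result under the first rule, leaves the reader unable to see the analysis as initially defined.
3. **Overlap with the main analysis.** A sensitivity analysis supports a conclusion only if it could have disagreed. If nearly all the same outcomes are reused, agreement says little.

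At stake is what the trial may say about exercise taken as prescribed. The intention-to-treat conclusion is not at stake.

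**Working it through.** **The plan's own figures.** Target exposure is 3 × 16 = 48 sessions, and 80% of 48 is 38.4, so a threshold of 39 is right. The unadjusted differences in eTable 3 reproduce from the arm means:
- Systolic: 126.93 − 125.83 = 1.10 and 127.81 − 125.52 = 2.29 (printed 2.30, rounding).
- Diastolic: 76.51 − 75.54 = 0.97 and 77.01 − 75.24 = 1.77.

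**Exclusions by arm (eTable 3 against eTable 2).** Exercise: 102 − 82 = 20 (19.6%). Control: 101 − 101 = 0.

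**Observed outcomes removed.** The two exercise strata of eTable 4 make up the whole arm (45 + 57 = 102 at baseline).
- At 16 weeks, 43 + 33 = 76 have a systolic value and eTable 3 keeps 71, so 5 of 76 (6.6%) are dropped.
- The arm lacks 102 − 76 = 26 values and the per-protocol set lacks 82 − 71 = 11, so 15 of the 20 excluded people had no 16-week value anyway.
- At 52 weeks, 35 + 33 = 68 against 63: again 5 dropped.
- With 84 controls in both tables, the overlap at 16 weeks is (71 + 84)/(76 + 84) = 155/160.

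**Effect on the unadjusted 16-week difference.**
- Systolic, all 76: (43 × 127.7 + 33 × 125.9)/76 = 126.92, so the difference from control is 126.92 − 125.83 = 1.09, against 1.10 per protocol.
- Diastolic, all 76: (43 × 77.0 + 33 × 75.7)/76 = 76.44, so the difference is 0.90, against 0.97.

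**Signs of selection.** The 20 dropped had a mean baseline diastolic pressure of (102 × 77.0 − 82 × 77.48)/20 = 75.0 mmHg (74.8 to 75.3 allowing for rounding), against 77.48 in those kept. The baseline systolic gap between arms goes from 129.1 − 128.3 = 0.8 to 129.41 − 128.25 = 1.16.

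**Plausible bias.** Bias is roughly the share excluded times the outcome gap between compliers and non-compliers. For an assumed gap of 5 mmHg it is 0.066 × 5 = 0.3 mmHg on observed values, or 0.196 × 5 = 1.0 mmHg on everyone excluded. A bias as large as the 5 mmHg design effect would need a gap of 5/0.196 = 25.5 to 5/0.066 = 76 mmHg.

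**An estimate that keeps both randomised arms.** The complier-average effect is approximately the all-randomised difference divided by the share compliant (82/102 = 0.804), with that share treated as fixed.
- Systolic, from 0.0 (−2.6, 2.7): 0.0 (−3.2, 3.4). The per-protocol result is 0.02 (−2.87, 2.92).
- Diastolic, reading the eTable 2 entry as 1.0 (−0.9, 2.9): 1.2 (−1.1, 3.6).

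**The case against.** The best defence is that this is labelled a sensitivity analysis, the trial's conclusion rests on intention to treat, and the change of definition is openly disclosed. Relaxing the definition also keeps more people and so moves the set towards the randomised one. All of that stands. Nothing suggests the change was driven by outcomes, and the protocol says outcome data are analysed by blinded operators. The protocol also defers detail to a statistical analysis plan that is not shown. The rule and its change may be recorded there, so their absence from the protocol is no fault.

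It is also fair that a complier-average estimate has assumptions of its own. With a yes/no threshold it supposes that allocation does nothing for anyone below 39 sessions. Partial adherence strains this, and so do the activity monitors, step target and feedback described in the protocol's Interventions section. Dividing by the exercise-arm share further supposes no equivalent exercise among controls. This is a reason to add the estimate with caveats and keep the table. The two systolic intervals above also come from different models (imputation and mixed model), so their widths are not strictly like for like.

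A reader might go further and take the 45 of 102 with at least 3 hours a week in eTable 4 as the supervised-only compliance rate. Dividing by 0.441 would give about −5.9 to 6.1 mmHg and suggest that the 5 mmHg design effect is not excluded. The documents do not support this:
- The stratum counts hours, not sessions. At 70 to 90 minutes each, 39 sessions over 16 weeks average 2.8 to 3.7 hours a week, a range that straddles the cut.
- The subgroup text describes supervised or unsupervised volume, while the table title says supervised.
- At least 82 − 45 = 37 people who met the relaxed rule would be assumed to have no effect.
- eTable 4 is labelled post-hoc exploratory.

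**Conclusion.** The point holds as a limit on what the per-protocol analysis can show. The exclusion is one-sided (20 of 102 against 0 of 101), the definition was relaxed during an open trial, and 155 of 160 observed participants are shared with the main comparison. Agreement was close to built in. The claim that it reinforces the main result goes beyond the evidence.

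The numerical effect is probably small: 0.01 mmHg on the unadjusted 16-week systolic difference, and 0.3 to 1.0 mmHg if compliers and non-compliers differ by 5 mmHg. A reader might infer from the 20 exclusions that the null result is in doubt, but 15 of those people had no 16-week value, and the intention-to-treat analysis does not depend on this set. At the reported compliance the complier-average interval (−3.2 to 3.4) still excludes a 5 mmHg fall.

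This rests on three assumptions: that the 20 excluded are the non-compliers, which no table states; that the eTable 3 set is a subset of the people in eTable 4; and that the compliance share can be treated as fixed. The supervised-only compliance rate is unknown, so no interval can be given for that definition.

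**What to change.** 1. Report the number compliant and the per-protocol results under the supervised-only definition first, then under the relaxed definition, labelled as changed during the trial. Give the date and reason of the change and whether it was made blind to outcome. State why each of the 20 was excluded.
2. Keep the per-protocol table and add a complier-average estimate on all randomised participants, with allocation as instrument for meeting the threshold, the same covariates, and the multiple imputation already used for missing outcomes.
3. State its assumptions: no effect of allocation below the threshold, and no equivalent exercise in controls. Give a supervised-only version only if the actual compliance rate under that rule is reported.
4. Replace the claim of reinforcement with wording such as: is consistent with, but not independent of, the main result.

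The cost is one extra model, a compliance count under the first rule (assuming session records separate supervised from unsupervised), and a few sentences. The price is a wider interval and assumptions stated in the open.
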